## Abstract

**Background::**

Benign prostatic hyperplasia (BPH) is the most common non-cancerous disease of the prostate and leads to lower urinary tract symptoms in middle-aged and elderly males. Fire needle therapy could improve the lower urinary tract symptoms associated with mild-moderate BPH in clinical practice. The aim of the present pilot study is to assess the preliminary effects of fire needle therapy on mild-moderate BPH.

**Methods::**

The present study is a prospective parallel randomized controlled pilot trial. A total of 60 eligible participants will be randomly assigned to a treatment or control group at a 1:1 ratio. The treatment group will receive fire needle therapy and the control group will receive watchful waiting with lifestyle advice and education regarding BPH. Participants will receive intervention for 4 weeks, with a follow-up period of 4 additional weeks. Adverse events will be recorded to assess the safety and tolerability of fire needle therapy for mild-moderate BPH. The primary outcome will be the change in the International Prostate Symptom Score. The secondary outcomes will include the change in the mean number of nightly urinations, the maximum urinary flow rate, the average flow rate, and the prostate volume as measured by a B-mode ultrasound device. All outcome measures will be observed at baseline and at 4 and 8 weeks following the beginning of treatment.

**Discussion::**

The present study will provide evidence of the preliminary effects of fire needle therapy on mild-moderate BPH and indicate an optimal sample size for future studies.

## Introduction

1

Benign prostatic hyperplasia (BPH) is a non-cancerous enlargement of the prostate gland, commonly encountered in middle-aged and elderly males.^[1]^ The main manifestation is an enlarged prostate and/or lower urinary tract symptoms (LUTS) without other known causes.^[2]^ LUTS is characterized by storage symptoms, such as urinary frequency, urgency, nocturia, and incontinence, in addition to voiding symptoms, such as hesitancy, progressive dysuria, and intermittent flow, and post-micturition symptoms, such as the feeling of incomplete emptying and post-micturition dribble.^[3]^ There is a positive correlation between the occurrence of BPH and age, and it often arises in males over the age of 40 years old.^[4]^ Studies have indicated that the prevalence of BPH is approximately 25% to 40% in men in their 50 s, about 50% in their 60 s, and more than 75% in their 80 s.^[4–7]^ Of the men who suffer from BPH, up to 50% experience LUTS.^[8]^ The prevalence of BPH in China is similar to that in western countries.^[9]^ Among Chinese urological outpatients, approximately 47.0% are men aged ≥60 with BPH.^[10]^ Studies have shown that Asians with BPH are more prone to suffer from moderate-severe LUTS than their American counterparts.^[11]^ Interventions for BPH include conservative (watchful waiting, behavioral and dietary modifications), pharmacological, and surgical treatments.^[12]^ Although BPH is not considered a risk factor for prostate cancer, it greatly influences patients’ health and quality of life and increases healthcare costs.

Acupuncture has a history of more than 2000 years in China and plays an important role in traditional Chinese medicine.^[13]^ The World Health Organization has composed a provisional list of diseases that could potentially be treated with acupuncture, 1 of which is prostatic disease.^[14,15]^ Recent systematic reviews have suggested that acupuncture has statistically significant beneficial effects on the International Prostate Symptom Score (IPSS) and maximum urinary flow rate (Q_max_) in moderate-severe BPH.^[16,17]^ Fire needle therapy was first recorded in Huangdi Neijing (The Inner Canon of Huangdi), 1 of the earliest medical books in China.^[18]^ It is an acupuncture technique that involves rapid insertion of a red-hot needle into the lesion or acupuncture point to eliminate disease symptoms.^[19]^ Outpatient fire needle therapy is widely used in the treatment of BPH and LUTS; however, high-quality clinical evidence is not yet available, especially that obtained using evidence-based design. Therefore, we designed this randomized controlled pilot trial to assess the preliminary effects of fire needle therapy on mild-moderate BPH and indicate an optimal sample size for future studies.

## Methods

2

### Study design

2.1

This is a prospective parallel randomized controlled pilot trial comparing fire needle therapy with watchful waiting. From July 1, 2020 to December 31, 2021, we will recruit patients suffering from mild-moderate BPH according to predefined inclusion and exclusion criteria. Participants will be randomly allocated to a treatment (fire needle therapy) or control (watchful waiting) group and receive treatment for 4 weeks. A 4-week follow-up will take place after the treatment period. All outcomes will be assessed at baseline and at 4 and 8 weeks following the beginning of treatment (Fig. 1).

**Figure 1 F1:**
[figure not shown]
Consolidated standards of reporting trials (CONSORT) flow chart of the present study. IPSS = International Prostate Symptom Score, ITT = intention-to-treat, PP = per-protocol, Q_ave_ = average flow rate, Q_max_ = maximum urinary flow rate.

### Sample size

2.2

Since there are no previous randomized controlled trials investigating this topic, the present study will be a pilot trial to provide effect size data for sample size calculations in subsequent large-scale randomized controlled trials. The sample size was not calculated based on a power calculation;^[20]^ instead, it was determined from estimates of the number of patients expected to participate and the minimum number of patients needed for an evaluation of the pragmatic purpose of the trial. Therefore, a total number of 60 participants, a sample size of 30 per group, will be recruited during the study, which is larger than the minimum number recommended for pilot studies.^[21]^

### Recruitment and baseline assessment

2.3

Researchers will recruit participants from outpatient clinics at the Department of Acupuncture and Moxibustion, Beijing Hospital of Traditional Chinese Medicine, Capital Medical University, Beijing, China. Recruitment information will be posted in the hospital, containing a brief introduction of the study, participants, interventions, and contact details, which will be pre-approved by the Institutional Review Board.

Patients who are interested in participating in the study will be provided with detailed written and verbal information, and those who volunteer to enroll will be asked to complete an IPSS questionnaire and a 2-week nocturia record and undergo a routine urine test, prostate ultrasound, and uroflowmetry test as a baseline assessment. The results will be used to decide whether to include the patients in the study according to the inclusion and exclusion criteria. All recruited participants will give their written informed consent with a witness present prior to the beginning of the study, and subsequently complete a general information form, including name, gender, age, and medical history. All participants will be treated respectfully according to the Declaration of Helsinki and will be able to withdraw from the study at any time for any reason. Personal information regarding the participants will be collected and kept confidential.

### Inclusion criteria

2.4

Patients are required to meet the following criteria:

(1)aged 40 to 80 years old;(2)diagnosed with BPH more than 3 months previously;(3)have a syndrome differentiation in traditional Chinese medicine conforming to “kidney yang deficiency;”^[22]^(4)have abstained from medication for BPH for longer than 6 months prior to the start of treatment;(5)have an IPSS score < 19 (mild-moderate BPH);(6)have a Q_max_ < 15 mL/s or a average flow rate  < 10 mL/s;(7)have stable life signs; and(8)participate voluntarily in the study and sign informed consent prior to treatment.

### Exclusion criteria

2.5

Patients with any of the following conditions will be excluded:

(1)oliguria and anuria caused by bladder or prostate malignancy, urolithiasis, or acute/chronic renal failure;(2)urinary dysfunction caused by neurogenic bladder, bladder neck fibrosis, or urethral stricture;(3)gonorrhea and urinary tract infection;(4)failure of invasive therapy for BPH;(5)local organ, muscle, or nerve injury caused by pelvic surgery or trauma;(6)abdominal aneurysms, hepatosplenomegaly, and serious cerebrovascular, cardiovascular, respiratory, digestive, hematological, or psychiatric diseases;(7)blood coagulation disorders or patients requiring administration of anticoagulant medication, such as warfarin or dabigatran;(8)cognitive dysfunction, psychosis, or patients who are unable to cooperate with the examination and treatment.

### Randomization and allocation concealment

2.6

Participants will be randomly assigned to 2 groups at a 1:1 ratio. The generation and allocation of a random sequence for group assignment will be conducted using the Statistical Analysis System (V.9.1.3; SAS Institute Inc., Cary, North Carolina) by the Research Center of Clinical Epidemiology, Beijing Hospital of Traditional Chinese Medicine, Capital Medical University, Beijing, China. Researchers involved in randomization will be blinded and will not take part in the recruitment and inclusion of participants. Opaque computer-generated sealed envelopes will be produced to conceal allocation. The envelopes will be numbered consecutively with a serial number on the outside and will contain the allocation information inside. An envelope will be opened as a participant is enrolled in the study following completion of the baseline assessments and written informed consent. Participants will be allocated to 1 of the 2 groups and receive the related intervention. The random allocation sequence and opaque sealed envelopes will be kept separately by 2 specific researchers.

### Blinding

2.7

The outcome assessors, data managers, and statisticians will remain blind to the participants’ group assignment. Acupuncturists, outcome assessors, data managers, and statisticians will not be allowed to communicate with each other regarding the participants’ allocation.

### Interventions

2.8

#### Treatment group

2.8.1

Participants in the treatment group will receive fire needle therapy in the outpatient clinics of the Department of Acupuncture and Moxibustion at the hospital. Interventions will be performed in accordance with the STRICTA.^[23]^ All acupuncturists will be registered practitioners of traditional Chinese medicine with at least 5 years of clinical experience. The fire needle treatments and manipulations will be standardized among acupuncturists using specific training. Fire needles (0.65 × 45 mm; Beijing Zhongyan Taihe Medical Instrument Co., Ltd., Beijing, China) will be used. Other medication for BPH will be prohibited during the trial.

The following acupoints will be used: CV4 (*guanyuan*), CV2 (*qugu*), and bilateral ST28 (*shuidao*). All acupoints will be located according to the World Health Organization Standardized Acupuncture Points Location.^[24]^ The manipulation of fire needle therapy will be conducted according to Chinese national standard Standardized Manipulations of Acupuncture and Moxibustion.^[19]^ During treatment, participants will maintain a supine position after urination. The acupoints will be sterilized twice, from the center to the outside of an imaginary circle with a diameter of 5 cm, using 75% alcohol, or 0.5% to 1% iodophor if an alcohol allergy is present. After the skin is dry, the tip and middle of the fire needle will be heated until it turns red, following which the acupoint will be directly penetrated by the needle to a depth of 25 mm. The needle will be subsequently withdrawn without retention after the therapeutic depth has been reached, and the puncture wound will be covered with a sterile cotton ball to avoid bleeding.

Treatment will be conducted twice per week. Participants will be treated once a day and will receive a total of 8 treatment sessions over 4 consecutive weeks.

#### Control group

2.8.2

Participants in the control group will receive watchful waiting, which is 1 of the conventional treatments suggested by both the Chinese and EAU Guidelines on the Management of Non-neurogenic Male LUTS.^[10,25]^ Watchful waiting and behavioral and dietary modifications are recommended as initial treatments for mild-moderate BPH (IPSS score < 19) in patients with non-bothersome LUTS. Accordingly, participants will receive education regarding BPH, reassurance regarding prognosis, and lifestyle advice once per week. Participants will receive a total of 4 outpatient visits over 4 consecutive weeks. Medication for BPH will be prohibited during the trial.

#### Follow-up

2.8.3

After the 4-week treatment, follow-up will be conducted among all participants for 4 weeks. Fire needle therapy and BPH-related treatment are not permitted during follow-up.

### Outcome measures

2.9

The primary outcome is the change in IPSS over the 2-week baseline, 4-week treatment, and 4-week follow-up periods. The secondary outcomes are the changes in the mean number of nightly urinations, Q_max_ and average flow rate, and prostate volume as measured by a B-mode ultrasound device over the 2-week baseline, 4-week treatment, and 4-week follow-up periods. All outcome measures will be observed at baseline and 4 and 8 weeks following the beginning of treatment (Fig. 2).

**Figure 2 F2:**
[figure not shown]
Schedule of enrolment, interventions, and assessments. IPSS = International Prostate Symptom Score, Q_ave_ = average flow rate, Q_max_ = maximum urinary flow rate.

### Adverse events

2.10

Adverse events will be recorded to access the safety of fire needle therapy. The common and expected adverse events include local hematomas, inflammation, bending of the needle, fainting, unbearable prickling, discomfort persisting for longer than 1 hour after acupuncture, local infections, abscesses, and local pruritus. All participants will receive a routine urine test and coagulation function test at baseline and at the end of the 4-week treatment period. Researchers will evaluate the relationship between adverse events and the interventions. All adverse events will be reported to the primary investigator and the Research Ethics Committee of Beijing Hospital of Traditional Chinese Medicine to decide whether the participants need to reveal allocated intervention and withdraw from the trial. The participants who experience adverse events will be treated with the relevant conventional therapy or hospitalization if necessary.

### Data management and monitoring

2.11

Researchers who manage data will be trained prior to enrollment. Assessors will be in charge of the acquisition of participant information and outcome assessment during the study. Data collectors will transfer the data from the case reports to electronic form. All paper and electronic data will be kept safely in the office of the Department of Acupuncture and Moxibustion. Only investigators of our study team can have access to the final trial data. Others getting written requests from the project administration can be allowed. The study will be regularly monitored and audited by the Data Management and Monitoring Committee of the Good Clinical Practice Department of Beijing Hospital of Traditional Chinese Medicine, Capital Medical University, Beijing, China. The committee is independent of the study researchers and has no competing interests; it will examine original case report forms, monitor the quality and completeness of the data, verify the recording of adverse events, and ensure that the study complies with the principles of the protocol. The periodic review is done every 3 months.

### Statistical analysis

2.12

The SPSS statistical package (version 20.0, International Business Machines Corporation, China) will be used to analyze the data. The primary outcome will be analyzed by both intention-to-treat and per-protocol analysis. The data missing from intention-to-treat analysis will be replaced with the last measured value. The secondary outcomes will be analyzed by per-protocol analysis. Categorical variables will be displayed as percentages. Continuous variables will be presented as the mean ± standard deviation if the data fit a normal distribution in 2 groups. Otherwise, the data will be presented as the median (interquartile range). The Kolmogorov–Smirnov test will be applied as the normal distribution test for continuous variables. The *t*-test or Wilcoxon test will be used to compare the difference between groups according to the results of the Kolmogorov–Smirnov test. The results for categorical data will be compared using the chi-squared test. The statistical significance level will be set at 0.05 (2-sided), with a 95% confidence interval.

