### Withdrawal and dropout

2.13

If participants use a combination of treatments that are prohibited by the study protocol, withdraw their consent, or cease communication, they will be excluded from the study. Researchers will report the reasons for withdrawal and dropout and acquire the time of last treatment and outcome measures where possible.

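### Carrying the last IPSS forward over only three visits biases the primary intention-to-treat effect, by an amount and in a direction that depend on dropout

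*Protocol article*

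**What the plan says.** The Statistical analysis section sets two analyses for the primary outcome: "The primary outcome will be analyzed by both intention-to-treat and per-protocol analysis". For the first it adds: "The data missing from intention-to-treat analysis will be replaced with the last measured value". No other imputation method, likelihood-based model or missing-data sensitivity analysis is named. The rule concerns only the primary outcome, since for the others "The secondary outcomes will be analyzed by per-protocol analysis".

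The schedule is short. Under Outcome measures, "All outcome measures will be observed at baseline and 4 and 8 weeks following the beginning of treatment", and "The primary outcome is the change in IPSS over the 2-week baseline, 4-week treatment, and 4-week follow-up periods"; no single primary time point is named. Men in the needle arm "will receive a total of 8 treatment sessions over 4 consecutive weeks", so week 4 is the end of treatment. Between weeks 4 and 8, "Fire needle therapy and BPH-related treatment are not permitted during follow-up".

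Under Withdrawal and dropout, men who use prohibited treatments, "withdraw their consent, or cease communication, they will be excluded from the study". The same section says researchers will try to obtain outcome measures when a man leaves, as far as they can. The Sample size section says that 60 men (30 per arm) was not a power-based number and that the pilot is to supply effect-size data for sizing later trials.

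**The concern.** With three measurements, carrying the last value forward can do only two things, and both impose a strong assumption.

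- **Loss before week 4, no exit measurement.** The last value is baseline, so the change is zero at weeks 4 and 8. The arm's mean change shrinks toward zero in proportion to its dropout.
- **Loss between weeks 4 and 8.** The end-of-treatment score stands in for a score four weeks after treatment stopped. This assumes that the effect persists in full over a period the trial otherwise observes.

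Neither needs dropout to be related to outcome: the bias arises even if men leave purely at random. The imputed scores are then analysed as though they had been observed. Because the estimate is meant to size later trials, an error here carries forward into their sample size.

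**Working it through.** The protocol gives no expected change, SD or dropout rate, so there is no figure to reproduce. All numerical inputs below are assumptions. Visits, treatment period and arm size (30) come from the protocol.

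**Formulas.** Let d be the share of an arm lost before week 4 with no exit value, e the share lost between weeks 4 and 8, and m4 and m8 the true mean changes. If dropout is unrelated to outcome, the expected mean change after carry-forward is

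- week 4: (1 - d) × m4
- week 8: (1 - d - e) × m8 + e × m4

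**Early dropout, week 4.** Assume -4 (needle) and -1 (control), a true difference of -3.0.

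- 20% v 10% (6 v 3 men): 0.8 × (-4) - 0.9 × (-1) = -3.2 + 0.9 = -2.3
- 10% v 20%: 0.9 × (-4) - 0.8 × (-1) = -3.6 + 0.8 = -2.8
- 5% v 20%: 0.95 × (-4) - 0.8 × (-1) = -3.8 + 0.8 = -3.0 (the errors cancel)
- 0% v 20%: -4 + 0.8 = -3.2 (exaggerated)

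**Late dropout, week 8.** Assume the needle effect fades from -4 to -2 and control stays at -1, a true week-8 difference of -1.0.

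- 10% in each arm: 0.9 × (-2) + 0.1 × (-4) - (-1) = -2.2 + 1 = -1.2
- 20% in each arm: 0.8 × (-2) + 0.2 × (-4) - (-1) = -2.4 + 1 = -1.4
- 10% early plus 10% late in each arm: [0.8 × (-2) + 0.1 × (-4)] - [0.8 × (-1) + 0.1 × (-1)] = -2.0 + 0.9 = -1.1

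**SD.** With true SD s and a share p set to zero, the arm's variance is (1 - p) × s² + p × (1 - p) × m². This exceeds s² when m² > s²/(1 - p).

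- s = 4, p = 0.2: the variance is understated unless the mean change exceeds √(16/0.8) = 4.5 points. For m = -4 it is 12.8 + 2.56 = 15.36 against 16.
- s = 3, p = 0.2, m = -4: 7.2 + 2.56 = 9.76 against 9, so it is overstated.

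**Effect on the next trial's N.** N scales with variance / difference². With s = 4:

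| Early dropout | Arm variances | Mean variance / 16 | Difference factor | N factor |
|---|---|---|---|---|
| 20% v 10% | 15.36, 14.49 | 0.933 | (3.0/2.3)² = 1.701 | 1.59 |
| 10% v 20% | 15.84, 12.96 | 0.900 | (3.0/2.8)² = 1.148 | 1.03 |

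N is about 59% or 3% too large. For late dropout with a fading effect, at constant SD, the factors are 1/1.2² = 0.69 and 1/1.4² = 0.51, so N is about 31% or 49% too small.

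**Type I error.** These come from 20,000 simulated trials of 30 per arm, with assumed SD 5, correlation 0.6 between weeks 4 and 8, and a two-sided t-test at 0.05.

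- Both arms truly change by -3, early dropout 20% v 5%: expected spurious difference 0.8 × (-3) - 0.95 × (-3) = 0.45; rejection rate about 6.5%.
- Needle -4 at week 4 relapsing to -1 at week 8, control -1 throughout, 20% late dropout in each arm: expected spurious difference -0.6; rejection rate about 7.3%.

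**The case against.** This is an unpowered pilot of 60 men that calls its findings preliminary. A per-protocol analysis of the primary outcome is also planned, an unseen analysis plan may add sensitivity analyses, and dropout may prove low. In the unfavourable null cases above, the type I error rises only modestly. All of this bears on severity. It does not remove the point: the method is positively chosen in the protocol, not left open. The per-protocol analysis is a second analysis set, not a way of handling missing data.

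A reader might infer more than the protocol supports.

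- **That every early leaver is scored as zero change.** This holds only where no outcome is obtained at withdrawal, and the protocol says researchers will try to obtain one.
- **That SDs and standard errors will be too small, leaving the next trial underpowered.** The direction for the SD depends on the mean change relative to the SD. The biased difference also enters the calculation. With early dropout on the assumptions used here, the net error is an N that is too large.
- **That unequal dropout is likely.** Participants are unblinded and the arms differ in visits and burden, so it is plausible in either direction. No figure in the protocol makes it likely.
- **That week 8 is the primary endpoint, there to test persistence.** The protocol names no primary time point and states no such purpose. Week 8 is one of two post-baseline visits.

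**Conclusion.** The concern holds in a limited form. As written, the rule gives a biased estimate for the primary intention-to-treat analysis whenever men are lost, apart from special cases where the errors cancel or the carried-forward value happens to equal the true mean. Early loss shrinks an arm's change; late loss imports an on-treatment score into an off-treatment visit. Under the assumed changes, the difference moves from -3.0 to -2.3 or -2.8 with early dropout. With late dropout and a fading effect, the week-8 difference moves from -1.0 to -1.2 or -1.4. The implied error in the next trial's N runs from about 59% too large to 49% too small. These figures rest on assumed means, SDs and dropout shares, on dropout unrelated to outcome, and on no exit measurement for early leavers. The actual size and direction cannot be known from the protocol. This should be fixed, but it does not invalidate the trial.

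**What to change.** In Statistical analysis, make the primary intention-to-treat analysis a likelihood-based repeated-measures model on all randomised men, using observed IPSS at baseline, week 4 and week 8, with arm, visit and arm-by-visit terms. Baseline can be one of the responses, so that a man with only a baseline value still contributes. Alternatively it can be a covariate, with multiple imputation for men who have no post-baseline value. Keep last-value carry-forward at most as a sensitivity analysis.

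In the same edit, reconcile Withdrawal and dropout with the intention-to-treat analysis. Excluding men who leave cannot stand beside an analysis of all randomised men, and it decides whose missing data are handled at all. State that data already collected from withdrawn men, including any exit measurement, are kept in the analysis.

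The cost is a short rewrite of two sections and slightly more analysis work, with no new visits or data. The downside is that the model relies on data being missing at random, which cannot be verified from the observed data.

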Selection of a control group is another major issue in planning the design of a study. We searched the Cochrane Central Register of Controlled Trials, MEDLINE, EMBASE, the Chinese Biomedical Database, the China National Knowledge Infrastructure, the VIP Database, and the Wanfang Database for clinical trials and systematic reviews describing acupuncture for BPH. As a result, the controlled intervention could be classified into 2 groups: sham acupuncture and medication. The use of sham acupuncture as a control was denied due to the clinical difficulty in performing sham fire needle manipulation. Since there is a lack of evidence supporting the use of fire needle therapy for BPH, we decided to use a blank control. After evaluating several guidelines for BPH and LUTS, we finally selected watchful waiting as the controlled intervention, which is strongly recommended for men with mild-moderate BPH (IPSS score < 19) who are minimally bothered by their symptoms.^[25]^ Should acupuncture prove to be effective in this study, we will subsequently compare fire needle therapy with a known medication as a positive control to clarify its specific effects.

However, the present study still has some unavoidable limitations. Despite the blinding of assessors, data managers, and statisticians, the therapists and participants cannot be blinded due to the nature of fire needle manipulation, which may lead to the occurrence of performance and detection biases. In addition, the 4-week treatment period with 8 treatments and the 4-week follow-up period are not sufficient to evaluate the long-term effects of fire needle therapy on BPH. Future trials should include more frequent treatments and a longer follow-up period to effectively investigate the long-term effects. Moreover, the sample size of this study is small, since it is proposed as a pilot for further studies. The results of the present study will offer preliminary data regarding the safety, tolerability, and effect of fire needle therapy for mild-moderate BPH and provide evidence for the optimal sample size in subsequent large-scale multi-center randomized controlled trials. The series studies of fire needle therapy will be a preliminary investigation into the potential enhancement of a currently used intervention and may contribute to changes in future clinical practice.

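### All four secondary outcomes are analysed per-protocol only, so their group comparisons are not protected by randomisation

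*Protocol article*

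**What the plan says.** Section 2.12 (Statistical analysis) sets the analysis populations by outcome. For IPSS: "The primary outcome will be analyzed by both intention-to-treat and per-protocol analysis". For the others: "The secondary outcomes will be analyzed by per-protocol analysis". The missing-data rule between these two sentences applies to the intention-to-treat analysis, which only IPSS has: "The data missing from intention-to-treat analysis will be replaced with the last measured value".

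Section 2.9 (Outcome measures) shows what the secondary rule covers. The list begins "The secondary outcomes are the changes in the mean number of nightly urinations" and continues with maximum flow rate, "average flow rate, and prostate volume as measured by a B-mode ultrasound device". That makes four outcomes, all measured at baseline, week 4 and week 8, as IPSS is.

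Section 2.13 (Withdrawal and dropout) gives the only stated rule for removing men from the trial after randomisation, cited here without its closing words: "If participants use a combination of treatments that are prohibited by the study protocol, withdraw their consent, or cease communication, they will be excluded from". It adds that reasons will be reported and that the last outcome measures will be obtained where possible. The Discussion acknowledges that "the therapists and participants cannot be blinded due to the nature of fire needle manipulation".

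**The concern.** A per-protocol comparison keeps only men who stayed on the plan, and staying on it is decided after allocation. Starting a prohibited BPH treatment can plausibly depend on symptoms and on knowing which arm one is in. The arms also ask different things of participants: eight needling sessions (section 2.8.1) against four advice visits (section 2.8.2). Most of the expected adverse events in section 2.10 belong to needling. The reasons for leaving may therefore differ by arm and be linked to outcome.

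The primary outcome is a questionnaire score from unblinded men. Flow rate and ultrasound volume, obtained by assessors who are to be blinded (section 2.7), are the natural corroboration. As planned, they have no analysis that keeps the randomised groups intact. The trial also exists to supply effect sizes for later trials (section 2.2), so a selected estimate would be carried forward.

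**Working it through.** **Step 1: is this a stated rule or an omission?** Section 2.12 names two analyses for IPSS and one for the secondary outcomes. The contrast makes per-protocol alone the natural reading. No other section gives a secondary outcome an intention-to-treat analysis. It is therefore a choice the article states, not a detail left to a fuller document.

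**Step 2: is there a plan figure to reproduce?** No. Section 2.2 gives 60 men, 60/2 = 30 per group, and says no power calculation was made. There is no effect size, SD or dropout rate. The sizes below rest on assumed exclusion shares and are illustrations only.

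**Step 3: upper bound.** Assume a normally distributed outcome with SD 1, exclusions in one arm only, and exclusion fully determined by outcome (correlation 1). Removing the worst share p shifts that arm's mean by φ(z)/(1 − p), where z is the 1 − p quantile and φ the normal density.

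- p = 0.10 (3 of 30): z = 1.2816, φ = 0.1755, shift = 0.1755/0.90 = 0.195 SD.
- p = 0.20 (6 of 30): z = 0.8416, φ = 0.2800, shift = 0.2800/0.80 = 0.350 SD.

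**Step 4: partial dependence.** If exclusion correlates ρ with a worse outcome, the shift is about ρ times the bound. For example, 0.5 × 0.195 = 0.098 and 0.5 × 0.350 = 0.175. A simulation of 20,000 trials (30 per arm, no true effect, two-sided t-test at 0.05, exclusions from the control arm only) agrees, with slightly smaller values at this sample size:

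| Excluded in one arm | ρ | Bias (SD) | Type I error |
|---|---|---|---|
| 0 | any | 0.00 | 0.048 to 0.050 |
| 10% (3 of 30) | 0 | 0.00 | 0.050 |
| 10% | 0.3 | 0.06 | 0.056 |
| 10% | 0.5 | 0.09 | 0.066 |
| 10% | 0.8 | 0.15 | 0.098 |
| 20% (6 of 30) | 0 | 0.00 | 0.048 |
| 20% | 0.3 | 0.10 | 0.068 |
| 20% | 0.5 | 0.17 | 0.099 |
| 20% | 0.8 | 0.27 | 0.186 |

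**Step 5: direction.** Removing the worst controls, for instance men who worsen and take medication, improves the control mean and works against fire needle. Removing the worst needle-arm men gives the same shift in its favour. Equal selection in both arms cancels. The article does not say which pattern to expect, so the sign is unknown.

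**The case against.** The strongest case on the other side has four parts.

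- **Per-protocol is not always biased.** With no exclusions it equals the as-randomised analysis, and with exclusions unrelated to outcome the bias is nil. Leaving because needling hurts need not select men with poor flow. This stands. A reader might infer that the randomised comparison is lost for everything except IPSS. The article supports only that its protection is removed, to a degree that depends on who is excluded and why. Nor does the point reach adverse events, which are not listed as a secondary outcome and have no stated analysis set.
- **The larger figures are worst cases.** This stands too. The 0.195 and 0.350 SD shifts need exclusion fully determined by outcome in one arm and none in the other. It is tempting to set 0.350 SD against the difference detectable with 80% power at 30 per arm (about 0.74 SD), but section 2.2 disclaims any power target, so that is not a benchmark of this trial.
- **A like-for-like set exists.** A reader might infer that primary and secondary results must describe different men. IPSS is also analysed per-protocol, so a comparison on the same type of set is available. What is missing is the as-randomised counterpart for the other four outcomes.
- **It is a pilot, and withdrawal reasons will be reported.** This lowers the severity but does not remove the point. Section 2.12 plans tests at the 0.05 level, the estimates are meant to inform later trials, and listed reasons show an imbalance without correcting it.

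**Conclusion.** The concern holds in a limited form. The article states a per-protocol-only analysis for all four secondary outcomes, alongside an exclusion rule that can depend on symptoms and known allocation. Those comparisons are therefore open to selection bias of unknown sign. Under the assumed one-arm exclusions and ρ of 0.3 to 0.8, the size is about 0.06 to 0.15 SD at 10% and 0.10 to 0.27 SD at 20%, with type I error of 0.056 to 0.098 and 0.068 to 0.186. The exclusion shares and ρ are assumptions. Severity: should fix. The IPSS intention-to-treat analysis and the sample size are unaffected by this point.

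**What to change.** **Section 2.12.** State that the secondary outcomes are analysed primarily in all randomised participants, in the assigned arm, using every observed week-4 and week-8 value, with per-protocol as supportive. Name a missing-data method, for example a baseline-adjusted mixed model valid under missing-at-random. Simply extending the IPSS intention-to-treat rule would bring last value carried forward into flow rate, volume and nocturia, which is not the aim.

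**Section 2.13.** Clarify that men who use prohibited treatment or stop the intervention stay in the analysis, with outcomes collected where possible and data kept as consent allows. Without this, the present exclusion wording would undercut the change in 2.12.

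**Cost.** Two short text changes, made before outcome data are seen. No extra participants or scheduled visits are needed, since all outcomes share the same visits and section 2.13 already seeks measures after withdrawal; some effort goes into following men who stop. Effects may look slightly smaller. The change mainly helps men who deviated but were still measured. Those with no post-baseline measurement still rest on the missing-data assumption.
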